**Sample Size Determination**

**We aim to power our study to detect a mean systolic blood pressure difference of 7 mmHg between study arms at the 6 months study visit. From baseline pilot data we expect a standard deviation around 17. With 80% power and a Type I error rate of 0.05, we estimate that we will need data on about 200 patients to be able to reject the null hypothesis of no difference between groups. Recognizing that there will be a reasonable rate of loss to follow-up, we plan to randomize 300 patients.**

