***5. Statistical Analysis:***

**STATISTICAL CONSIDERATIONS**

**Statistical Hypotheses**

- Primary Efficacy Endpoint(s):
  - Hypothesis: The mean decrease in systolic blood pressure from baseline to the 6 month study visit will be 5 mmHg greater in the intervention group relative to the control arm.
- Secondary Efficacy Endpoint(s):
  - Hypothesis 1: Systolic blood pressure will be 5 mmHg lower in the intervention group relative to the control arm at 3 months post randomization, measured pragmatically.
  - Hypotheses 2: Diastolic blood pressure will be 5 mmHg lower in the intervention group relative to the control arm at 3 months (measured pragmatically) and 6 months (study visit) post randomization.
  - Hypothesis 3: The proportion of patients having achieved blood pressure control (as defined by a BP < 140/90) will increase by 10% in the intervention group relative to the control group.

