**Statistical Analyses**

***General Approach***

For descriptive statistics, we will present continuous data as means with standard deviation or median with interquartile range, as appropriate. Categorical data will be presented as percentages. For inferential tests, we will use a p-value of 0.05 as the cutoff for statistical significance; tests of hypothesis will be two-tailed.

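### The primary hypothesis is a 5 mmHg systolic difference but the sample size is set for 7 mmHg; at 5 mmHg and SD 17, power is 54% to 72%, not 80%

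*Protocol*

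**What the plan says.** All of this is in the Protocol.

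- **Hypothesised effect.** Under Statistical Hypotheses, the primary hypothesis is that the mean fall in systolic pressure from baseline to the 6-month visit "will be 5 mmHg greater in the intervention group relative to the control arm".
- **Powered effect.** Sample Size Determination states: "We aim to power our study to detect a mean systolic blood pressure difference of 7 mmHg between study arms", again at the 6-month visit.
- **Design inputs.** The source of the SD is given: "From baseline pilot data we expect a standard deviation around 17". Power is set at 80% and alpha at 0.05, and the section concludes: "we estimate that we will need data on about 200 patients".
- **Number randomised.** To allow for losses, the section says "we plan to randomize 300 patients". No loss rate is given.
- **Test.** General Approach says that "tests of hypothesis will be two-tailed". The primary endpoint section plans t-tests on change from baseline, together with a linear regression. Allocation is 1:1.

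No section says why the trial is sized for 7 mmHg when it predicts 5 mmHg, and none calls 7 mmHg a minimum important difference.

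**The concern.** Both figures describe the same quantity. One is worded as a difference in change and the other as a difference at 6 months, but under randomisation the two have the same expected value. The protocol therefore gives two targets for one comparison, and the one used for sizing is 40% larger than the one predicted (7/5 = 1.4).

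This matters most if the programme works as predicted. A reader who finds 5 mmHg in one section and 80% in the next may join them. If the true effect is 5 mmHg, a non-significant result is much more likely than the 20% such a reader would assume, and it could be taken as evidence that the programme does not work. Type I error, the estimand and the planned analysis are not affected.

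**Working it through.** **Inputs.** Differences of 7 mmHg (Sample Size Determination) and 5 mmHg (Statistical Hypotheses); SD 17; two-sided alpha 0.05; 1:1 allocation; 200 patients with data; 300 randomised. Applying SD 17 to the change score is an assumption.

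**1. The plan's own figure.** By the normal approximation, n per arm = 2 × SD² × (1.960 + 0.842)² / d². For d = 7 this is 2 × 289 × 7.849 / 49 = 92.6, so 93 per arm and 186 in total. The t-test (noncentral t) gives 188. The protocol's figure of about 200 is 6 to 7% higher, which looks like a cautious rounding up.

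**2. Power at 200 and at 300 analysed.** The standard error of the difference is SD × √(4/N): 17 × √(4/200) = 2.404 and 17 × √(4/300) = 1.963. The noncentrality is d/SE.

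| Analysed | d (mmHg) | d/SE | Power (t-test) |
|---|---|---|---|
| 200 | 7 | 2.91 | 82.6% |
| 200 | 5 | 2.08 | 54.4% |
| 300 | 7 | 3.57 | 94.5% |
| 300 | 5 | 2.55 | 71.9% |

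The normal approximation gives 82.9%, 54.8%, 94.6% and 72.1%.

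**3. Number needed at 5 mmHg.** 2 × 289 × 7.849 / 25 = 181.5, so 182 per arm and 364 in total. The t-test gives 366, which is more than will be randomised.

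**4. Difference detectable with 80% power (SD 17, t-test).** 6.8 mmHg with 200 analysed and 5.5 mmHg with 300.

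**5. Precision.** The expected 95% confidence interval half-width with 200 analysed is 1.972 × 2.404 = 4.7 mmHg. An observed difference of 5 mmHg would only just reach significance, which is why power at a true 5 mmHg is little above one half.

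**6. Sensitivity to the SD (assumed values, d = 5, t-test).**

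| SD | 200 analysed | 300 analysed |
|---|---|---|
| 14 | 71% | 87% |
| 15 | 65% | 82% |
| 17 | 54% | 72% |
| 18 | 50% | 67% |
| 20 | 42% | 58% |

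Power of 80% at 5 mmHg needs an SD of about 12.6 with 200 analysed, or about 15.4 with 300. If 17 is the SD of a single reading, and is equal at both times, the SD of change is 17 × √(2(1 − r)), where r is the correlation between baseline and 6 months. It equals 17 only when r = 0.5. The protocol gives no r.

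**The case against.** The strongest reply is that the sample-size calculation is correct for what it claims. The 80% is tied to 7 mmHg and is met with a margin, and no sentence claims 80% power at 5 mmHg. A trial may be designed around a difference other than the one it expects. This stands in part: a reader might infer that the calculation is wrong, or that the stated 80% is really 54%, and the document supports neither. What remains is that the choice is neither declared nor justified, and that the powered effect is larger than the expected one, which is not the cautious direction.

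A second reply is that 54% is the low end. The 200 is the number needed, not a forecast of retention, and the protocol gives no loss rate. This stands. A reader might infer a trial that amounts to a coin flip, but that describes only the case of 200 analysed; with complete follow-up at SD 17 power is 72%, still below 80%.

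A third reply is that the SD is uncertain. It comes from baseline pilot data, while the endpoint is change from a baseline that averages the last two readings. This also stands. A reader might infer that 5 mmHg cannot reach 80% power even with complete follow-up. That is true at SD 17, but not at an SD of about 15.4 or less. The uncertainty runs both ways, since an SD above 17 makes the shortfall worse.

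Finally, the trial is called a minimal-risk pilot. Its stated purpose is nevertheless to test effectiveness, with a formal power statement and a significance test, so the power at the hypothesised effect is relevant.

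**Conclusion.** The point holds as an internal inconsistency between the hypothesised and the powered effect, with no error in the 7 mmHg calculation. If SD 17 applies to the change score, and with a two-sided 0.05 t-test, power at the hypothesised 5 mmHg is 54% with 200 analysed and 72% with 300. Confidence in the mismatch is high, because both numbers are in the text. Confidence in any single power figure is lower, because it depends on the number analysed and on an SD of change that is not given; across the assumed SDs of 14 to 20 and 200 to 300 analysed, power at 5 mmHg runs from 42% to 87%. It should be fixed, ideally before results are seen, but it does not undermine the validity of the test or the estimate.

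**What to change.** Keep 300 randomised and reconcile the two sections. In Sample Size Determination:

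- State that, at SD 17, 200 analysed gives 80% power for about 6.8 mmHg (83% for 7 mmHg), and 54% for the hypothesised 5 mmHg, or 72% with all 300 analysed.
- Say whether SD 17 refers to a single reading or to change. If it is a single reading, give the SD of change, or a range for it, with the power that follows.
- State that a non-significant result will be interpreted from the 95% confidence interval, with an expected half-width of about 4.7 mmHg at 200 analysed.

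If 7 mmHg is kept as the design target, justify it and still report the power at 5 mmHg. Raising the hypothesis to 7 mmHg without doing so would make the sections agree but hide the shortfall.

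The cost is one paragraph of wording and a less favourable power statement. It needs no extra patients and no change to the analysis.

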**Statistical Analyses**

***General Approach***

For descriptive statistics, we will present continuous data as means with standard deviation or median with interquartile range, as appropriate. Categorical data will be presented as percentages. For inferential tests, we will use a p-value of 0.05 as the cutoff for statistical significance; tests of hypothesis will be two-tailed.

***Analysis of the Primary Efficacy Endpoint(s)***

The primary analysis will be an intention to treat analysis among those that met inclusion criteria and were randomized to the intervention or control arm. The primary endpoint will be a continuous measure of change in blood pressure from baseline to the 6 month study visit. Crude between group differences will be assessed using t-tests. We will also use a linear regression model. While randomization should create balance between arms, if there is any residual imbalance in covariates deemed to be associated with the outcome, these will be adjusted for to enhance efficiency. These may include: age, sex, race, ethnicity, payor group, Charlson comorbidity index. Patients enrolled in the intervention arm will be included in the analysis even if they opt out of the texting intervention (intention-to-treat). In addition, we will conduct a secondary per-protocol analysis including only those patients randomized to the intervention who completed enrollment, and ultimately received equipment and messages.

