## *Data Analysis*

## The baseline is the mean of last two BP. The final BP is the one taken at the six month visit.

**RISK/BENEFIT ASSESSMENT:**

***1. Risks:***

We consider this study minimal risk. The primary risk would be from a breach of confidentiality involving medical record reviews and monitoring of hypertension medication and blood pressure measurement adherence with text messaging which will be maintained on the Way to Health platform. This risk has been mitigated by extensive privacy protection protocols, a highly secure data storage system, and a plan to remove identifiers from the data wherever possible. In addition, all personnel will be held to high standards of upholding confidentiality and safeguarding patient privacy

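### The primary analysis of change in systolic BP does not commit to adjusting for baseline systolic BP; the test is valid, but it gives up precision that the data already collected could supply.

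*Protocol*

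**What the plan says.** The protocol, under Analysis of the Primary Efficacy Endpoint(s), sets the scale: "The primary endpoint will be a continuous measure of change in blood pressure from baseline to the 6 month study visit". The method follows: "Crude between group differences will be assessed using t-tests. We will also use a linear regression model". Adjustment in the regression depends on residual imbalance being found in covariates thought to be related to outcome. The candidates are given as: "These may include: age, sex, race, ethnicity, payor group, Charlson comorbidity index". Baseline blood pressure is not among them. Under Baseline Descriptive Statistics, mean baseline blood pressure is listed first and the covariates are then brought in as additional items, so the protocol appears to treat the two as separate.

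Under Data Analysis the baseline is fixed: "The baseline is the mean of last two BP". The final value is the one from the 6-month visit.

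Under Sample Size Determination the aim is to "detect a mean systolic blood pressure difference of 7 mmHg between study arms at the 6 months study visit", and the variability input is: "From baseline pilot data we expect a standard deviation around 17". About 200 evaluable patients are said to be needed and 300 are to be randomised. No SD of change and no baseline-to-final correlation is given.

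**The concern.** Baseline systolic BP would usually be the strongest available predictor of 6-month systolic BP. A change score uses it with a fixed coefficient of 1. ANCOVA estimates the coefficient, and for large samples its residual variance is never larger. The protocol says that adjustment is meant to improve efficiency, yet it makes adjustment conditional on observed imbalance (the efficiency gain does not need imbalance) and does not name the covariate most likely to deliver it.

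There is also a mismatch of scale. The sample size is framed as a difference in level at 6 months, with an SD from baseline data, while the test is on change. If 17 is the SD of a single-time reading, it does not give the SD of change without a correlation. What is at stake is power and the width of the confidence interval, not the validity of the test.

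**Working it through.** **Inputs from the protocol.** Difference 7 mmHg, SD 17, 80% power, type I error 0.05 (Sample Size Determination); two-sided tests (General Approach); 1:1 allocation; about 200 evaluable, so 100 per arm.

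**Assumed, because the protocol does not give them.** The correlation ρ between baseline and 6-month systolic BP; the baseline SD, σ_b; and a 6-month SD, σ_f, of 17.

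**Step 1: the plan's own figure.** n per arm = 2(1.96 + 0.842)² × 17² / 7² ≈ 92.6, so 93 per arm and 186 in total; the exact t calculation gives 94 per arm, 188 in total. The stated figure of about 200 is a little above this and reads as rounding up. At 100 per arm with SD 17 the t-test has 82.6% power. There is no error here.

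**Step 2: formulas.**
- SD of change = √(σ_b² + σ_f² − 2ρσ_bσ_f). With both SDs at 17 this is 17√(2(1 − ρ)).
- ANCOVA residual SD = σ_f√(1 − ρ²), which does not depend on σ_b.
- Variance ratio, change score to ANCOVA = 1 + (σ_b − ρσ_f)² / (σ_f²(1 − ρ²)). It is never below 1. With equal SDs it is 2/(1 + ρ).

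**Step 3: power at 100 per arm, 7 mmHg, σ_f = 17 (t-test).**

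| σ_b | ρ | SD of change | Power, change | ANCOVA SD | Power, ANCOVA | Variance ratio |
|---|---|---|---|---|---|---|
| 17 | 0.3 | 20.11 | 68.8% | 16.22 | 85.9% | 1.54 |
| 17 | 0.4 | 18.62 | 75.3% | 15.58 | 88.5% | 1.43 |
| 17 | 0.5 | 17.00 | 82.6% | 14.72 | 91.7% | 1.33 |
| 13 | 0.4 | 16.77 | 83.6% | 15.58 | 88.5% | 1.16 |

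Last row: 13² + 17² − 2 × 0.4 × 13 × 17 = 169 + 289 − 176.8 = 281.2, and √281.2 = 16.77. The ANCOVA variance is 289 × 0.84 = 242.8, and 281.2/242.8 = 1.16.

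**Step 4: the correlation that the change score needs.** At 100 per arm, 80% power requires an SD of change of at most 17.58. Solving for ρ: ρ ≥ (17² + σ_b² − 17.58²) / (2 × 17 × σ_b).

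| σ_b | 12 | 13 | 14 | 15 | 16 | 17 |
|---|---|---|---|---|---|---|
| Minimum ρ | 0.30 | 0.34 | 0.37 | 0.40 | 0.43 | 0.47 |

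If all 300 were analysed, the equal-SD minimum falls to about 0.20. ANCOVA has no such condition: its residual SD is at most 17, so power at 100 per arm is at least 82.6% for any ρ.

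**Step 5: does eligibility on high readings lower change-score power?** Take an unselected SD of 17 and ρ = 0.4, so the slope is 0.4 and the residual variance 242.8. Let selection cut the baseline SD to 12, with slope and residual variance unchanged. The variance of change becomes (1 − 0.4)² × 144 + 242.8 = 294.6, so the SD is 17.16. The correlation drops to 0.29, yet power rises from 75% to 82%. A lower correlation produced by truncation is therefore not evidence of lower power.

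**The case against.** The strongest reply is that nothing is invalid. Under randomisation the t-test on change is unbiased and keeps its type I error. Regression to the mean acts on both arms equally in expectation, and chance baseline imbalance is already reflected in the standard error. That stands, and it limits the point to precision. A reader might infer that selecting patients on high readings, or a chance imbalance, makes the primary result biased; the design does not support that.

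A second reply is that the covariate list is open-ended, so baseline BP is not excluded, and an SAP that is not shown may name it. This stands in part. But the protocol does more than leave a detail open: it names a crude test on change, makes adjustment conditional on imbalance, and lists candidates without baseline BP.

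A third concerns the planning SD. Reading 17 as a single-time SD is an inference from its source in baseline data, and the protocol does not label it. If 17 were already the SD of change, power at 200 would be about 83% with no condition on the correlation. Even then, baseline adjustment would be at least as precise in large samples.

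It is tempting to say that the stated power holds only if the correlation is at least 0.47. That figure needs an SD of 17 at both times and exactly 200 analysed. The baseline here is a mean of two readings in patients selected on blood pressure, so its SD may well be below 17, and the threshold moves with it. Nor does the documents' eligibility rule show that selection reduces power; Step 5 gives a case where it raises it.

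**Conclusion.** The concern holds as a matter of efficiency. The primary analysis as written is valid but does not secure the precision available from a baseline already defined and collected. In the cases tabulated, the change score carries 16% to 54% more variance than ANCOVA, and at 100 per arm its power is about 5 to 17 percentage points lower. These figures rest on an assumed 6-month SD of 17, baseline SDs of 13 or 17 and correlations of 0.3 to 0.5, none of which the protocol settles.

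On the likelier reading of the SD of 17, 80% power for the change score with 200 analysed requires an unstated correlation of at least about 0.30 to 0.47, for baseline SDs from 12 to 17. ANCOVA meets the target at any correlation. This should be changed before analysis, but it does not threaten the validity of the trial or call for more patients. The protocol also hypothesises a 5 mmHg effect while powering for 7; that is a separate matter, and 7 is used throughout here.

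**What to change.** - **Primary analysis:** name ANCOVA as the single primary analysis: 6-month systolic BP (or its change, which gives the same treatment estimate) regressed on arm and baseline systolic BP, with baseline always included whether or not imbalance is seen. Report the adjusted difference with its 95% confidence interval. Keep the t-test on change as a descriptive supplement.
- **Secondary endpoints:** treat diastolic BP the same way with its own baseline, and include baseline blood pressure in the logistic model for BP control.
- **Sample Size Determination:** state whether 17 is the SD of a single-time systolic BP or of change. If single-time, add that the calculation is conservative under ANCOVA; if of change, give its source.

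The cost is protocol and SAP wording only. No new data are needed and the sample size does not change.

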***Analysis of the Secondary Endpoint(s)***

Secondary endpoints will include the change in systolic blood pressure at 3 months post randomization; change in diastolic blood pressure measured at 3 months and 6 months; and blood pressure control (<140/90) at 6 months. The statistical approach for continuous measures will be similar to that described above. For the binary outcome of blood pressure control, crude differences will be assessed with a chi-squared test, and we will use a logistic regression model with adjustment for covariates as described above.

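### Adjusting the primary model only for covariates found to be imbalanced does not serve the precision aim given for it; the covariates should be fixed in advance and include baseline SBP and PCP

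*Protocol*

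**What the plan says.** The Protocol, under Analysis of the Primary Efficacy Endpoint(s), takes the change in blood pressure from baseline to the 6-month visit, analysed by intention to treat. Two analyses follow: "Crude between group differences will be assessed using t-tests. We will also use a linear regression model". Covariates enter the regression by a condition: "if there is any residual imbalance in covariates deemed to be associated with the outcome, these will be adjusted for to enhance efficiency". The candidates are introduced as possibilities: Charlson index, payor, ethnicity, race, sex and age. No threshold defines imbalance and no criterion defines association with the outcome.

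Two variables are absent from that list. One is baseline systolic pressure, although the Data Analysis section defines a baseline for every patient. The other is PCP, although Study Design and Method for Assigning Subjects to Groups both stratify the randomisation by it.

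The secondary endpoints inherit the approach. For blood pressure control, "we will use a logistic regression model with adjustment for covariates as described above". General Approach sets the level: "we will use a p-value of 0.05 as the cutoff for statistical significance; tests of hypothesis will be two-tailed". Sample Size Determination aims to "detect a mean systolic blood pressure difference of 7 mmHg between study arms at the 6 months study visit" and adds "From baseline pilot data we expect a standard deviation around 17".

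**The concern.** The rule and its purpose do not match. A strongly prognostic covariate that happens to be balanced would be left out, although including it would shrink the residual variance. PCP is the clearest case: stratification balances it by design, so a rule that waits for imbalance would hardly ever admit it.

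The rule also makes the model depend on the data. Whether a covariate enters turns on an undefined degree of imbalance and an undefined judgement of association, so two analysts could follow the text and fit different models.

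At stake are some avoidable loss of power, a test that does not hold its nominal level exactly, and a modest opening for choosing between results.

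**Working it through.** **Inputs from the protocol.** Difference 7 mmHg, SD 17, two-sided 0.05, 80% power, about 200 evaluable patients (100 per arm), six listed covariates.

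**Assumptions, not in the protocol.** The covariates jointly explain R² = 0.1 to 0.3 of outcome variance. They are independent, normal and equally predictive. Imbalance means p < 0.10 for the arm comparison of a covariate or, alternatively, a standardised difference above 0.2.

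**Step 1: the plan's own figure.** n per arm = 2(1.960 + 0.842)² × 17² / 7² = 2 × 7.85 × 289 / 49 = 92.6, so 93 per arm and 186 in total (188 with the t distribution). The plan's figure of about 200 is slightly higher, which is on the safe side and no part of this point. At 100 per arm the standard error is 17 × √(2/100) = 2.404. Then 7/2.404 − 1.960 = 0.952, which gives power of 82.9% without adjustment.

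**Step 2: what fixed adjustment offers.** Residual SD = 17 × √(1 − R²). Observed imbalance does not appear in this formula.

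| R² | Residual SD | Power at 100 per arm |
|---|---|---|
| 0.1 | 16.13 | 86.6% |
| 0.2 | 15.21 | 90.2% |
| 0.3 | 14.22 | 93.6% |

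**Step 3: how often the trigger fires.** With p < 0.10, each covariate enters in 10% of trials by chance, and at least one of six enters in 1 − 0.90⁶ = 47%. With p < 0.05 the latter is 1 − 0.95⁶ = 26%. So in about half of trials or more the regression would contain no covariate at all.

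**Step 4: simulation.** 100 per arm, trigger at p < 0.10, with 20,000 trials under no effect and 8,000 at 7 mmHg for each R².

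| | R² = 0.1 | R² = 0.3 |
|---|---|---|
| Type I error, crude | 5.0% | 5.0% |
| Type I error, triggered | 4.6% | 3.7% |
| Type I error, fixed | 5.0% | 4.7% |
| Type I error, better of crude and triggered | 5.6% | 5.7% |
| Power, crude | 83.2% | 82.1% |
| Power, triggered | 83.5% | 84.0% |
| Power, fixed | 85.8% | 92.5% |
| SD of estimate (mmHg), crude / triggered / fixed | 2.41 / 2.37 / 2.31 | 2.41 / 2.25 / 2.03 |

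Before rounding, the power forgone by the trigger is 85.82 − 83.45 = 2.4 points at R² = 0.1 and 92.47 − 84.00 = 8.5 points at R² = 0.3. The variance of the fixed estimate relative to the triggered one is (2.31/2.37)² = 0.95 and (2.03/2.25)² = 0.81.

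The triggered test is conservative because, when the covariates are balanced, the crude estimate varies less than its standard error says: that standard error still carries the covariates' share of the variance.

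**Step 5: a looser trigger.** A standardised difference above 0.2 at 100 per arm corresponds to z = 0.2/√(2/100) = 1.41, so more covariates enter. Type I error of the triggered test alone was then 3.4 to 4.9% across the settings run. The loss against fixed adjustment was about 2, 5 and 6 points at R² = 0.1, 0.2 and 0.3. The better of crude and triggered gave 5.4 to 6.3%.

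**The case against.** The strongest defence is that a protocol need not settle the final model. Which of two listed analyses decides, and the exact covariate list, are ordinary content of a statistical analysis plan, which may exist. The wording also leans towards the t-test: it comes first, the regression is added to it, and the sample size uses an SD with no allowance for adjustment. That much stands. A reader might infer that the trial has no primary test, but the documents do not support treating this as a defect, since an analysis plan could name one.

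The defence does not reach the trigger. The protocol states that rule, with its purpose, and an analysis plan with a fixed covariate set would have to override it.

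Two further points are fair. Power under the triggered rule stays above 80% in every setting run, so what is lost is a gain beyond plan, in a trial that calls itself a pilot. And imbalance is judged on baseline data, which can be inspected before any 6-month outcome is seen, so the rule is not inherently driven by outcomes. Only the undefined judgement of association leaves that open.

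**Conclusion.** The point holds as a worthwhile improvement, not as a threat to the trial's validity. The trigger works against its stated aim and costs about 2 to 8 points of power at 7 mmHg relative to a fixed model, for R² between 0.1 and 0.3. Used alone, it is slightly conservative. The figures rest on the assumed R², the assumed definition of imbalance and simple simulated covariates. They concern the linear model; the logistic model was not simulated.

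Two stronger readings are tempting and not supported:

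- **Substantial inflation of type I error.** Choosing between the crude and an always-adjusted model would give 6.7 to 7.5%, and choosing the best of all 64 covariate subsets 9.9 to 14.2%. The protocol offers no always-adjusted model beside the triggered one and describes no such search. For the two analyses it does describe, the figure is about 5.5 to 6%, and only if the more favourable result is the one reported.
- **A loss equivalent to 25% more patients.** At R² = 0.2 fixed adjustment removes 20% of the variance, and 1/(1 − 0.2) = 1.25. That compares fixed adjustment with none, whereas the triggered rule already recovers part of the gain.

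**What to change.** Replace the conditional sentence with one primary linear model for change in systolic pressure. Its terms are arm, baseline systolic pressure, PCP (or practice, if PCP strata are sparse) and those prognostic covariates that the team selects in advance from the existing list. State that all of them are included whatever the observed balance, and that the set is fixed before any outcome data by arm are examined. A moment tied to unblinding would have no meaning here, because the trial is not blinded. Whether PCP or practice is used can be settled from stratum sizes alone.

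Label the crude t-test as supportive. Apply the same rule to the secondary endpoints, with baseline diastolic pressure for the diastolic outcomes.

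The cost is a few sentences. Baseline pressure is already defined, PCP is known from randomisation, and the listed covariates are already planned for the baseline description. No further patients or data are needed.
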